#### Data management

2.4.1

The principal investigator (PI) [12] will have the main responsibility for the monitoring of the data but data will be registered by the research study investigators. Furthermore, the PI will ensure the design of the trial and will have overseen for data integrity and data security.

### Statistical analysis

2.5

The primary analysis principle applied will be the intention-to-treat. All statistical analysis and data management will be performed using SPSS for Windows, version 28.0 (IBM, Armonk, NY, USA). Measurements, such as XSS score, TEWL, pH, impedance, abundance of the biomarkers will be used as continuous variables and treatment with the creams, gender, and patients grouping parameters will be used as categorical variables. Descriptive statistics such as number of participants, mean, median, standard deviation, minimum and maximum values will be summarized and tabulated. XSS score will be independently evaluated by a random sample of twenty photographs by a second dermatologist, for validation purposes, to be able to assess inter-rater reliability by calculating intraclass correlation with 95 % confidence intervals. The primary outcome of the study is to compare the change in XSS score from baseline until the end (4 weeks) due to treatment with moisturizing creams vs a comparator product. Prior to analysis of the XSS differences between the treatment groups, the distribution of the data will be tested for normality by performing Shapiro-Wilk and Kolmogorov-Smirnov tests, as well as inspecting quantile-quantile (QQ) plots. Homogeneity of variances will be tested by performing Levene's test. Comparison between two related groups, *e.g.*, application of the formulation on the left and right foot, will be done by paired two-sample *t*-test, whereas for unrelated two groups two-sample *t*-test will be performed. When neither homogeneity of variances nor assumption of normality will be fulfilled, a non-parametric Wilcoxon rank sum test will be applied. In case of comparison between more than two groups, *e.g.*, the effect of three creams, one-way ANOVA with multiple comparisons (Tukey's test) will be used. Alternatively, if assumptions of normality or homogeneity of variances will not be fulfilled, non-parametric Kruskal Wallis test will be performed. The effect of covariables, *e.g.*, age, on main effect, *e.g.*, XSS change upon the treatment with the cream, will be tested by performing ANCOVA analysis. To seek for the measurements capable to explain and predict the effectiveness of the diabetic foot treatment with different creams more complex statistical analysis will be performed. Principal component analysis (PCA), multiway ANOVA and mixed models, and multiple regression analysis and model selection will be performed on the data collected. Level of statistical significance was set to p<0.05.

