#### Inclusion criteria

2.2.1

•Persons above 18 years of age diagnosed with any type of diabetes mellitus, with self-experienced dry skin.•Dry skin on both feet with a Xerosis Severity Scale (XSS) [15] score between two to six. No more than one XSS score in difference between the subjects' feet.•Ability to understand sufficient Swedish language to complete the necessary forms and understand the procedure of the study.

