#### Sample size estimation

2.2.4

This is a superiority RCT, where either of the intervention creams is hypothesized to be superior to the comparator cream in reducing XSS score during a four-week application period. To be able to prove this hypothesis, a total of 98 participants, 39 persons with diabetes in each arm for analysis, is needed, which is based on the following: A change in XSS score ≤1 is not regarded clinically important. The estimated intra-individual standard deviation for the difference in XSS score is 2.0. With 80 % power, two-tailed significance of 2.5 % in every arm, 39 evaluable study persons is needed in every arm, a total of 78 persons. If 20 % of persons are estimated not to be fully evaluable, sample size increases to 98 (78/0.8).

The following formula will be used to calculate the number of patients needed in each part of the trial [15,16] (N = number of fully evaluable patients in each part of the trial):$$N=\frac{\sigma_{d}^{2}\times {\left(\lambda_{\alpha }+\lambda_{\beta }\right)}^{2}}{\Delta^{2}}$$In the formula above σ_d_ is the standard deviation for the difference between the change in each treatment, Δ is the difference to detect between the treatments (a difference of at least 1 is assumed to be clinically relevant), λ_x_ is the x:th percentile of the standardized normal distribution. As the test is two-sided and the significance level should be 0.0250 (in order to keep the family-wise type I error at 5 % and there are two comparisons: Canoderm® versus Decubal® and Oviderm® versus Decubal) then λ_α_ = 2.1414. If the power is 80 % then λ_β_ = 0.8416 and if the power is 90 % then λ_β_ = 1.2816.

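### The paired t-test on week-4 XSS change fixes the baseline slope at 1, gives the day-14 score no role and, without imputation, may fall short of ITT; a baseline-adjusted repeated-measures model would gain modest precision

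*Protocol article*

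**What the plan says.** The relevant statements in the protocol article are these.

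- **Principle** (2.5 Statistical analysis): "The primary analysis principle applied will be the intention-to-treat".
- **Outcome and test** (2.5): the primary outcome is the change in XSS from baseline to four weeks. For two related groups the example is "application of the formulation on the left and right foot, will be done by paired two-sample" t-test. One foot gets the intervention cream and the other the comparator, so the primary comparison in each arm is of this kind.
- **Sample size** (2.2.4): N counts fully evaluable people, and 20 % of "persons are estimated not to be fully evaluable, sample size increases to 98 (78/0.8").
- **Eligibility** (2.2.1): "No more than one XSS score in difference between the subjects' feet".
- **Schedule** (2.3.1.1, 2.4 and Table 2): XSS is graded at baseline, day 14 and day 28.
- **Other models** (2.5): ANCOVA is named for covariables, with age as the example. Mixed models are named for explaining and predicting treatment effectiveness. Neither is tied to baseline XSS, to day 14 or to the primary comparison.
- **Attrition** (3 Discussion): the article recognises a risk of attrition bias, from people who live far away and from elderly people with more comorbidity.

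**The concern.** Three features of the stated test deserve attention.

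1. **Who enters.** A paired t-test on baseline-to-week-4 change needs a week-4 score. Unless values are imputed, anyone without one drops out of an analysis described as intention-to-treat, including a person who was graded at day 14.
2. **How baseline enters.** The difference in change scores equals the week-4 between-foot difference minus the baseline between-foot difference, which is adjustment with the slope fixed at 1. XSS is an integer grade that the Discussion calls not always clear-cut, so part of a one-category difference at baseline may be grading noise. A slope below 1 is then plausible, and the fixed slope leaves avoidable variance. Age as a covariate does not replace this adjustment, because its common effect on both feet cancels within the person.
3. **What is unused.** The day-14 score is the only post-baseline XSS for a person lost between day 14 and day 28, and it has no stated role in the primary comparison.

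At stake are some precision and the fit between the stated principle and the stated test.

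**Working it through.** **Inputs from section 2.2.4.** Significance level: "As the test is two-sided and the significance level should be 0.0250". Standard deviation: "The estimated intra-individual standard deviation for the difference in XSS score is 2.0". Difference to detect: 1. Power and size: "With 80 % power, two-tailed significance of 2.5 % in every arm, 39 evaluable study persons is needed in every arm, a total of 78 persons".

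**The plan's own figure.** N = σ²(z_α + z_β)²/Δ². With the two-sided 0.025 quantile of 2.2414 and 0.8416 for 80 % power, N = 4 × (3.0830)² = 38.02, rounded up to 39. Then 78/0.8 = 97.5, rounded up to 98. Both figures reproduce. The quantile printed in the article, 2.1414, gives 4 × (2.9830)² = 35.6, or 36. It looks like a misprint, which is a separate matter.

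**Starting power.** The formula is a normal approximation. The paired t-test itself (noncentral t, 39 pairs, SD 2.0, difference 1, two-sided 0.025) has 78.1 % power.

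**Baseline adjustment.** Let D0 and D28 be the between-foot differences at baseline and day 28, v0 the variance of D0, and b the slope of D28 on D0. The change contrast is D28 − D0, so

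Var(D28 − D0) = residual variance + (1 − b)² × v0.

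With the left side held at 2.0² = 4, adjustment removes the share (1 − b)² × v0 / 4. The documents give neither v0 nor b, so both are assumed. Eligibility limits D0 to −1, 0 or 1. With a mean of zero, v0 is then the proportion of people whose feet differ.

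| v0 | b | Share of variance removed | Power at 39 pairs |
|---|---|---|---|
| 0.3 | 0.7 | 0.09 × 0.3 / 4 = 0.7 % | 78.4 % |
| 0.5 | 0.3 | 0.49 × 0.5 / 4 = 6.1 % | 80.9 % |
| 0.67 | 0 | 1 × 0.67 / 4 = 16.8 % | 85.7 % |

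The degrees of freedom spent on one or two covariates change these powers by less than 0.3 percentage points. At b = 1 the removed share is zero.

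**Day-14 data.** Take 98/2 = 49 randomised per arm and assume that 10 of them (20 %, rounded) lack a week-4 score, that m of those 10 have a day-14 score, and that the day-14 and day-28 differences correlate at ρ. A likelihood analysis has effective size

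n_eff = 1 / [(1 − ρ²)/39 + ρ²/(39 + m)].

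- ρ = 0.3, m = 5: 1 / (0.91/39 + 0.09/44) = 39.4, power 81.5 %.
- ρ = 0.7, m = 10: 1 / (0.51/39 + 0.49/49) = 43.3, power 85.3 %.

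These powers use the normal approximation, under which 39 pairs give 81.1 %. They should be compared with that figure and not with 78.1 %.

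**The case against.** Several stronger readings are tempting, and the documents do not support them.

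- **That the analysis is restricted to completers.** The article does not say so. A paired t-test can be run after imputation, and a condensed article commonly leaves missing-data rules to the full protocol or SAP. Their absence is no finding. What stands is conditional: without imputation, the named test uses only people with a week-4 score.
- **That the baseline difference between feet is ignored.** It is subtracted. Foot allocation is randomised and the difference is at most one category, so the change score is a valid analysis. Only its efficiency is in question.
- **That about 20 of 98 people will be lost.** The 20 % are people not fully evaluable. The article does not say that they lack a day-28 score. Some may have deviated from the protocol yet been measured, and under ITT they would stay in. Twenty people is an upper bound, and the sample size already allows for it.
- **That the expected attrition biases the cream contrast.** The reasons given are distance, age and comorbidity. These act on the person and remove both feet together. Bias in the within-person contrast would need dropout to depend on the difference between the feet.
- **That baseline XSS is excluded as a covariate.** Age is only an example for ANCOVA, and age could still modify the cream difference.

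It is also fair to say that omitting day 14 from a week-4 endpoint is not an error in itself, and that choosing between a change score and ANCOVA is partly preference. The top of the power range needs about two thirds of participants to have unequal feet and a slope of zero. These objections limit the size of the point. They do not remove it, because the adjusted model uses data already planned and is at least as efficient apart from a negligible loss of degrees of freedom.

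**Conclusion.** The point holds as a modest improvement to a valid primary analysis. Baseline adjustment would remove about 1 to 17 % of the variance and move power at 39 pairs from 78 % to about 78 to 86 %. This assumes a baseline-difference variance of 0.3 to 0.67, a slope of 0 to 0.7 and an SD of the change contrast of 2.0. Little or nothing is gained if the slope is near 1. Using day 14 would raise the effective size from 39 to between 39.4 and 43.3 per arm, under the assumed dropout and correlations. The documents give none of the variances, slopes or correlations needed to narrow these ranges. Separately, if missing week-4 scores are not imputed, the stated test may not meet the stated ITT principle for some of the up to 20 % not fully evaluable. No systematic bias from baseline is claimed.

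**What to change.** For each arm, at two-sided 0.025, make the primary analysis a mixed model for repeated measures:

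- **Response:** within-person XSS difference (intervention foot minus comparator foot) at days 14 and 28.
- **Terms:** visit, baseline between-foot difference and centred baseline mean XSS of the two feet, with each covariate allowed its own effect by visit.
- **Population:** all randomised people with any post-baseline score.
- **Primary estimate:** the day-28 contrast.
- **Sensitivity analysis:** the paired t-test on baseline-to-week-4 change.

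If the full protocol or SAP already has a rule for missing week-4 scores, it should be reconciled with this model and with the ITT statement.

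The cost is analysis wording and one model in SPSS MIXED. Section 2.5 already names mixed models and treats XSS as continuous, and no further data are needed. There are two downsides: the estimate relies on a missing-at-random assumption, and people with no post-baseline score still do not contribute.

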#### Enrollment and randomization

2.2.3

Persons with diabetes will be introduced about the study at society meetings and at social media. Potential study participants that are suitable (according to the study criteria) for the study will be contacted and informed in more details about the study by the research nurses. Furthermore, a welcome letter will be sent by post to the participants with practical information. If acceptance and pass of criteria, informed consent form will be signed and the potential participants will be recorded in the research software program Research Electronic Data Capture® (REDCap) version 13.1.37. The participants will then be randomized and will adhere to the clinical study schedule and specific study procedures. The enrolled study participants will be given an autonomic code (in REDCap) as soon as the participants have signed the consent form. According to the code the participants will be randomized into different treatment, unknown which, for both the participants and the investigators (double-blind). Apart from the treatment randomization the participants will be randomized to which foot that will be treated with which cream. One foot will be treated with one interventional cream (cream A or B) and the contralateral foot with the comparator humectant-free cream (C).

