##### Primary outcomes

2.3.1.1

The primary outcome in this study, which the power calculations are based on, is the change in xerosis (dry skin), after four-week application of creams containing humectant compared to humectant-free cream on the diabetic feet. XSS score will be assessed and evaluated at baseline, i.e., visit 1 or 2 (if washout period needed), visit 2/3 (after two weeks after baseline-week application) and visit 3/4 (four weeks after baseline). Assessment will be performed using the 7-graded (from 0 to 6) XSS score. The classification of the scale is described in Table 1. Foot xerosis severity will be determined based on the most severe located dryness of the foot, and this location will be documented in REDCap.

**Table 1 tbl1:** The xerosis severity scale.

Classification	Description	Category
Mild	Normal Skin	0
	Dusty appearance, occasional minute skin flakes	1
	Generalized dusty appearance, many minutes skin flakes	2
Moderate	Defined scaling with flat borders	3
	Well defined heavy scaling with raised borders, shallow fissures	4
Severe	Large scale plates, fissures	5
	Large scale plates, deep erythematous fissures	6

Digital photographs with Canon EOS (Electro-Optical System) 750D, Canon Inc, Tokyo, Japan of the participants' feet will be taken for documentation in REDCap to be objectively evaluated by a dermatologist, and for XSS validation, by a second dermatologist. The Canon EOS 750D is capable of producing great photos and has been updated with a 24.2 megapixel sensor and built in Wi-Fi making it an excellent entry level DSLR (digital single-lens reflex camera). In a report published in 2018, a DSLR camera was successfully used to visually classify heel xerosis grade using similar xerosis assessment scale as outlined in the present study protocol, and to evaluate the effects of moisturizer on heel skin dryness [23]. The dermatologists will not have any personal contact with the study participants and will be blinded to cream exposure to evaluate dryness of the feet.

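### Section 2.5 lets assumption pre-tests, including a Levene test that paired data do not need, choose the test for the primary within-person XSS comparison and can send it to an unpaired rank test

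*Protocol article*

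**What the plan says.** The primary outcome is the change in XSS from baseline to four weeks (sections 2.3.1.1 and 2.5). Each participant treats one foot with Oviderm or Canoderm and the other with Decubal (section 2.2.3), so each primary comparison is within person. The score is an integer: "Assessment will be performed using the 7-graded (from 0 to 6) XSS score".

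Section 2.5 makes the test depend on the data. Before the XSS differences are analysed, the data are to be "tested for normality by performing Shapiro-Wilk and Kolmogorov-Smirnov tests, as well as inspecting quantile-quantile (QQ) plots", and "Homogeneity of variances will be tested by performing Levene's test". Related groups, with left and right foot as the example, get a paired t-test and unrelated groups a two-sample t-test. One sentence then gives the way out for both: "When neither homogeneity of variances nor assumption of normality will be fulfilled", a Wilcoxon rank sum test is used.

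For comparisons of more than two groups there is a separate rule. ANOVA gives way to Kruskal-Wallis "if assumptions of normality or homogeneity of variances will not be fulfilled".

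Section 2.2.4 sizes the trial with a paired formula: SD of the difference 2.0, difference 1, two-sided 0.025 for each of two comparisons, 80 % power, 39 evaluable per arm.

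**The concern.** Three features of this gate fit the primary comparison badly.

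- **No deciding rule.** Two formal normality tests and a plot are named, and nothing says which prevails. Differences of a 0-6 integer score are discrete and heavily tied, so formal tests often reject on granularity alone.
- **An irrelevant condition.** The paired t-test works on one difference per person and assumes nothing about equal variances in the two feet. Yet the two-group sentence makes failure of equal variances part of the trigger for paired feet.
- **A fallback that drops the pairing.** The rank sum test is for independent samples. The design and the sample size both rest on pairing.

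At stake is that the primary test is settled only after the data are seen, can differ between the Oviderm and Canoderm comparisons, and can be one for which the 39 per arm was not calculated.

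**Working it through.** **1. The plan's own figure.** From section 2.2.4, N = SD² × (λα + λβ)² / Δ², with SD 2.0, Δ 1 and λβ 0.8416. With the two-sided 0.025 quantile 2.2414: 4 × (2.2414 + 0.8416)² = 4 × 9.505 = 38.02, rounded up to 39. Two arms give 78, and 78/0.8 = 97.5, so 98. The stated size is reproduced. (The article prints λα as 2.1414, which would give 4 × 2.983² = 35.6; 39 matches 2.2414.) The calculation presumes a paired analysis. The exact paired t-test power at n = 39 is 78.1 %.

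**2. Which rule governs the primary test.** Each primary comparison involves two creams on related feet, so only the two-group sentence applies. Read literally, both normality and equal variances must fail before the test changes.

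**3. Simulation of that rule.** From the documents: 39 pairs, integer scores 0-6, outcome test at two-sided 0.025. Assumed, because the article does not give them: the baseline distribution, the between-foot correlation, pre-tests at 5 %, Kolmogorov-Smirnov with Lilliefors correction, normality tested on the paired differences, and Levene on the two feet's changes. There were 4000 trials per scenario. Entries from the third row down are % of trials; pairs are Shapiro-Wilk / Kolmogorov-Smirnov as the deciding normality test.

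| | No effect | Effect A | Effect B | Effect C |
|---|---|---|---|---|
| SD of difference; mean benefit | 2.10; 0 | 1.98; 0.95 | 1.94; 0.89 | 1.70; 0.78 |
| Between-foot correlation | 0.08 | 0.08 | 0.29 | 0.18 |
| Normality rejected | 21.6 / 59.8 | 29.9 / 67.5 | 37.1 / 75.9 | 46.2 / 82.4 |
| The two normality tests disagree | 41.9 | 41.3 | 41.9 | 40.1 |
| Levene rejects | 6.0 | 21.8 | 18.8 | 13.5 |
| Switch to rank sum | 1.1 / 3.5 | 6.7 / 14.7 | 7.5 / 14.8 | 6.2 / 11.1 |
| Significant, paired t always | 2.6 | 73.9 | 70.9 | 70.1 |
| Significant, rule as written | 2.6 / 2.6 | 73.5 / 72.7 | 69.4 / 67.9 | 69.4 / 68.9 |
| Significant, signed-rank always | 2.4 | 72.0 | 69.8 | 68.3 |
| Significant, rank sum always | 2.0 | 70.6 | 55.1 | 61.9 |

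A second simulation, under its own assumptions, switched in about 3-5 % of trials with equal creams and 11-17 % with a true effect, and lost at most about 1 point of power. Taking both together, the normality tests disagree in roughly 35-45 % of trials at SDs of about 1.6-2.0.

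**4. What the table shows.**
- Power lost to the rule as written: 73.9 − 72.7 = 1.2, 70.9 − 67.9 = 3.0 and 70.1 − 68.9 = 1.2 points with Kolmogorov-Smirnov deciding; 0.4, 1.5 and 0.7 points with Shapiro-Wilk.
- Levene is the limiting condition. In scenario C with Kolmogorov-Smirnov, normality fails in 82.4 % of trials but the switch occurs in 11.1 %, close to Levene's 13.5 %. Near SD 2, Levene rejects in 6.0 % with equal creams and 18.8-21.8 % with an effect, so the switch is likelier when a cream works.
- Where the switch occurs, the unpaired test is the cost. In scenario B, always using rank sum gives 55.1 % power, against 70.9 % for paired t and 69.8 % for signed-rank. In a further no-effect scenario with correlated feet, rank sum rejected in 0.1 % of trials and paired t in 2.5 %.

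**5. Different tests in the two arms.** The arms contain different people. If each switches independently with probability p, exactly one switches with probability 2p(1 − p): 2.0 % at p = 0.01, 9.5 % at p = 0.05 and 28.2 % at p = 0.17.

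**The case against.** The strongest reply is that the rule that actually applies does little. It switches rarely, costs about a point of power and does not raise the false-positive rate. Levene's test has a proper place in section 2.5 for unrelated groups and ANOVA. Which normality check decides is detail that a journal article may leave to an analysis plan. All of this stands as a limit on the size of the point. It does not remove it: the article itself states the gate, applies it to XSS, and writes one fallback sentence that does not separate paired from unpaired data.

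A reader might infer more from the section, in three ways.

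- *The trigger for the primary test is stated twice, once as both assumptions failing and once as either.* The documents do not support this. The either-fails wording belongs to comparisons of more than two groups. The two rules differ in logic, and the same meaning may have been intended for both, but that would be a guess. Switching rates and power losses calculated under an either-fails rule therefore do not describe the primary test.
- *Control of the 0.025 level is lost.* In the no-effect scenario the rule as written rejected in 2.6 %, the same as the paired t-test; with correlated feet it rejected in 2.4 %. The rank sum test errs on the conservative side.
- *The choice of trigger alone costs much power.* Near SD 2.0, with a signed-rank fallback, even the both-fail and either-fails rules reached different conclusions in at most about 2 % of trials. Most of the loss seen with rank sum comes from ignoring the pairing.

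**Conclusion.** The point holds in limited form. Section 2.5 makes the primary test data-dependent, leaves the normality decision open between checks that often disagree on this kind of score, lets an irrelevant variance test act as the limiting condition for paired feet, and names an unpaired fallback. Expected harm is small: a switch in about 1-5 % of trials with equal creams and up to about 17 % with a true effect, a power loss of about 1 point in most scenarios and 3 in the worst, and no inflation of type I error. What remains is that the two primary comparisons may be tested differently and that a comparison which switches loses its pairing. The percentages depend on the assumed baseline distribution and between-foot correlation (about 0.1-0.6 across the scenarios run); the reading of the text does not. The gate also gains little, since the paired t-test alone had a simulated type I error of 2.0-2.6 % against the nominal 2.5 %.

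**What to change.** In section 2.5, state that each primary comparison (Oviderm versus Decubal, Canoderm versus Decubal; within-person difference in XSS change to week 4) is tested by the paired t-test at two-sided 0.025, whatever the normality or variance checks show. Name the Wilcoxon signed-rank test as the sensitivity analysis in both arms. Drop Levene's test for left-right comparisons and keep QQ plots as description only.

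This is a change of wording, to be made before unblinding. It needs no further participants or data and matches the paired basis of the 39 per arm. The only thing given up is the freedom to change the test after seeing the distribution; the signed-rank analysis covers that, with nearly the same simulated power (69.8 % against 70.9 % in scenario B).

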## Discussion

3

The prevalence of diabetes mellitus is increasing in the world, 537 million adults suffer from this condition, and it is estimated to raise [1]. DFU is a devasting complication, ending up in major amputation and shorter life-expectancy for many. Prevention for DFU is therefore a global priority.

Better foot care with hydration may result in healthier feet but also to better vigilance of foot status in persons with diabetes. To be able to show differences in change in skin xerosis when using creams containing humectant compared with humectant-free cream on dry feet in persons with diabetes, might lead to specific recommendations for products that can be used for prevention of DFU. Furthermore, the results of this study can fill the gap of lack of documented effect when using different creams for persons with diabetes.

A potential limitation of this RCT could be that persons with diabetes accepting and attending this study is among those with most healthy feet in a population of diabetes, a well-known phenomenon in population-based screening studies [31]. Consequently, there is a risk that XSS scores at baseline are at the lower range, close to 2, where there is not much room for improvement by intense foot hydration with any of the creams. Determination of XSS scores is not always clear-cut and there may be discrepancies between raters. Therefore, we plan to perform an inter-rater reliability assessment, where twenty randomly selected photographed feet are selected and assessed by two independent dermatologists. The study protocol with at least three visits may for some participants be difficult to comply with, and there is a risk for attrition bias, where persons living far away from the centrally located research centre in Malmö, or elderly with higher degree of comorbidity, drop out from the study. The strengths are the design of two-armed double-blinded RCT, where the patients both feet are randomized, one receiving one of the intervention creams and the contralateral foot by default receiving the comparator cream. In this way, the participants feet act as a perfect matched pair of intervention-control, where patient-related factors are identical. Comprehensive evaluation of skin integrity barrier, microcirculation and neuropathy during the study period will hopefully result in advance in the understanding of disturbances of dry feet in persons with diabetes, and how to counteract.

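### The only two-group non-parametric fallback is the rank sum test for independent samples, although the primary comparison is between two feet of the same person

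*Protocol article*

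**What the plan says.** Section 2.2.3 (Enrollment and randomization) gives each participant one intervention cream on one foot and the humectant-free comparator on the other. The Discussion presents this as a strength: "the participants feet act as a perfect matched pair of intervention-control, where patient-related factors are identical". Section 2.2.4 (Sample size estimation) sizes each arm as a set of pairs, using the SD of the within-person difference (2.0) and a difference of 1 between treatments. On alpha it says "As the test is two-sided and the significance level should be 0.0250".

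Section 2.5 (Statistical analysis) announces normality tests and Levene's test before the XSS differences between treatment groups are analysed. It then assigns the parametric tests: "Comparison between two related groups, *e.g.*, application of the formulation on the left and right foot, will be done by paired two-sample" *t*-test, and a two-sample *t*-test for unrelated groups. A single fallback sentence follows: "When neither homogeneity of variances nor assumption of normality will be fulfilled, a non-parametric Wilcoxon rank sum test will be applied". No signed-rank test or other paired rank test is named anywhere in the article.

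**The concern.** The Wilcoxon rank sum (Mann-Whitney) test assumes two independent samples. The two feet of one person are not independent, and the design relies on that. With positively correlated changes, the rank sum test uses too large a variance for the difference. Its type I error then falls below the nominal level and it loses power. The matching test is the Wilcoxon signed-rank test on the within-person difference.

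The condition for the fallback has a similar fault. Levene's test compares the variances of two groups, but equal variance between the feet is not an assumption of the paired *t*-test, so it should not help decide how the paired comparison is analysed.

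Non-normality is a realistic prospect. The outcome is a coarse integer scale ("Assessment will be performed using the 7-graded (from 0 to 6) XSS score"), and the Discussion itself expects baselines near 2 with little room to improve. At stake is the chance of detecting the one-category effect for which the trial was sized. There is no added risk of a false positive claim.

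**Working it through.** **Inputs from section 2.2.4:** SD of the within-person difference 2.0, difference 1, two-sided alpha 0.025 per comparison, 80 % power, 39 evaluable pairs per arm. **Assumption:** the between-foot correlation ρ of the changes, which the documents do not give, is varied from 0 to 0.7.

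**1. The plan's own figure.** N = σ_d²(λ_α + λ_β)²/Δ² = 4 × (2.2414 + 0.8416)² = 38.02, rounded up to 39. Two arms give 78, and 78/0.8 = 97.5, rounded up to 98. Both figures reproduce. (The section prints λ_α as 2.1414, which would give 35.6, so 36. The stated 39 therefore rests on the correct 2.2414.) The exact power of the paired *t*-test at 39 pairs is 78.1 % (81.1 % by the normal approximation). With scores rounded to integers it is about 76 %.

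**2. What ignoring the pairing does.** With the SD of the difference fixed at 2.0, the SD of change on each foot is 2/√(2(1−ρ)). The paired standard error is 2/√39 = 0.320. An unpaired test instead uses 0.320/√(1−ρ). To a normal approximation, the power of an unpaired test is Φ(√39/2 − 2.2414/√(1−ρ)), with √39/2 = 3.1225, and its true type I error is 2[1 − Φ(2.2414/√(1−ρ))]. For ρ = 0.5: 2.2414/0.7071 = 3.170, so power = Φ(−0.047) = 48 % and type I error is about 0.15 %.

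**3. Simulation of the rank sum test itself** (39 pairs, integer-rounded scores):

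| Assumed ρ | SD per foot | Unpaired power by formula | Rank sum power, simulated | Rank sum type I error, simulated |
|---|---|---|---|---|
| 0 | 1.41 | 81 % | about 76 % | 2.8 % |
| 0.3 | 1.69 | 67 % | about 60 % | 0.8 % |
| 0.5 | 2.00 | 48 % | about 43 % | 0.2 % |
| 0.7 | 2.58 | 17 % | about 16 % | 0.01 % |

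Repeated runs vary by about two points. The signed-rank test on the same data keeps about 73 to 76 % at every ρ.

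**4. How often the fallback would be used.** The figures in step 3 apply only when the rank sum test is actually run. For the rule as a whole (rounded normal scores, both checks at an assumed 5 % level, ρ = 0.3, 0.5, 0.7):

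- *Both checks must fail (the literal reading).* This happens in 1.1, 0.6 and 0.2 % of trials if normality is tested on the paired difference, and in 4.1, 1.7 and 0.5 % if it is tested on each foot's change. In the second case power under the rule is 75.1, 75.2 and 75.7 %, against 75.7, 75.9 and 76.0 % if the paired *t*-test is always used. The loss is under 1 point.
- *Either failure is enough.* Shapiro-Wilk alone rejects the rounded paired differences in about 27 % of trials. Power under the rule is about 61 to 67 %, and moves by a few points with the variable on which normality is tested.

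**The case against.** Four points weigh on the other side.

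- **The trigger is narrow.** A reader might infer that trial power drops from about 78 % to between 40 and 65 %, or that the fallback will often be used. The documents do not support either. The sentence, read literally, requires both assumptions to fail, and under rounded normal scores they seldom do so together. This stands, and it limits the size of the problem. It does not settle the matter, because the Kruskal-Wallis rule in the same section is triggered when either assumption fails. An analyst could well apply both rules in that way.
- **The sentence may be meant only for unrelated groups.** It comes directly after the two-sample *t*-test, for which the rank sum test is the right fallback. That reading is possible, but the sentence carries no such limit. It would also leave the paired primary comparison with a normality check and no rule for failing it.
- **It may be a slip for signed-rank.** It may be, but the two are different tests, and an analyst following the text would run the wrong one.
- **The error is conservative.** This is correct: type I error falls below 2.5 %. The cost is power in a superiority trial.

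The power figures also depend on a correlation that the documents do not state. A positive value is what the matched-pair argument presumes, but at zero almost nothing is lost.

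**Conclusion.** The stated fallback does not fit the paired primary comparison, and Levene's test does not belong in the condition for it. If the rank sum test is used there, power is about 60, 43 and 16 % at assumed correlations of 0.3, 0.5 and 0.7, against about 76 % for the paired *t*-test and about 74 % for the signed-rank test. For the rule as a whole, the loss is about 1 point on the literal reading, while power is about 61 to 67 % if either failed check triggers the fallback. These whole-rule figures assume rounded normal scores. Floor effects on the 0 to 6 scale would change how often the checks fail. The stronger reading, that the plan as written forfeits a third or more of its power, holds only if the rank sum test is always run. This is a should-fix correction of a wrongly named test. It leaves the sample size and the type I error control intact.

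**What to change.** In section 2.5, for left-right comparisons, replace the rank sum test with the Wilcoxon signed-rank test on the within-person difference in XSS change. Keep the rank sum test for comparisons between arms only. Remove Levene's test as a condition for the paired comparison, and state that any normality check applies to the within-person difference. Removing the normality gate altogether, with the paired *t*-test fixed as primary and signed-rank as a sensitivity analysis, is an option and not required by this point.

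The change takes one or two sentences in the protocol or analysis plan and should be made before unblinding. It needs no new data and no change to the sample size.
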